##### Total response rates

We will compare the total response rates between the two groups. Meanwhile, we will perform a subgroup analysis by different operation types of Billroth-I, Billroth-II, or Roux-en-Y reconstruction. In fact, some researchers reported that Roux-en-Y reconstruction could destroy the natural small-bowel pacemaker [20–22]. Subgroup analysis of laparoscopic and open surgery will also be included in our results.

#### Secondary outcome measures

##### Endoscopic features

DGE patients may have chronic inflammation of the upper digestive tract. Thus, endoscopy will be performed to determine reflux esophagitis, gastritis, and gastric stasis in the remnant stomach. We will compare the ratios of reflux esophagitis, gastritis, and gastric stasis between the two groups.

##### Autonomic function

An electrocardiogram (ECG) will be performed on the first day and the last day of this trial, and it will assess the sympathetic and parasympathetic activities using the spectral analysis of heart rate variability (HRV). We will calculate the ratios of the low-frequency (LF) band and high-frequency (HF) band of the HRV signal, which can assess the autonomic function of the patients. A few studies have shown that electroacupuncture improves clinical outcomes via vagal activation [23–25]. ECG can assist us in revealing the mechanism of the effects of TEA on DGE.

##### Nutritional status

The change in serum albumin and body mass index (BMI) will be recorded for nutritional status screening and evaluation. Additionally, the scored patient-generated subjective global assessment (PG-SGA) (weight, food intake, symptoms, activities and function, disease state, metabolic demand, and nutritional physical examination) will be used to quickly identify malnutrition status, and patients will be scored as A (well-nourished), B (moderately malnourished or suspected malnutrition), and C (severely malnourished).

##### Psychological status

Depression and anxiety symptoms will be assessed using the Hospital Anxiety Depression Scale (HADS). The HADS is a reliable self-rating scale questionnaire with seven items (scored from 0 to 3). A total HADS score over 10 indicates positive outcomes (moderate to severe symptoms).

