### Sample size

Based on a previous electroacupuncture study on gastric emptying function, the response rate is approximately 50–70% [26–30]; however, the data of sham electroacupuncture are insufficient. Thus, we assumed that the response rates of the TEA group and sham-TEA group were 50% and 20%, respectively. Therefore, Δ is 30%. We estimated the sample size using the following formula:
$$ n=\frac{2{\left({\mu}_{\alpha }+{\mu}_{\beta}\right)}^2P\left(1-P\right)}{\Delta ^2} $$

A sample size of 66 patients will give us a power of 90% (*β* = 0.1) with a two-sided significance level of 0.05 (*α* = 0.05). To compensate for a 20% expulsion rate, a total of 90 patients will be required for the study. We will design a ratio of 2:1 (60 patients in the TEA group, 30 patients in the sham-TEA group) based on the response rates of the two groups.

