### Statistical analysis

Sensitivity analysis will be performed to determine the impact of incomplete records on the results. Intent-to-treat analysis of the results will be performed if there is nonadherence or missing data. Only two data statisticians will have access to the final trial dataset, which will only contain coded data, and they will perform statistical analysis using the SPSS version 22.0 software. Student’s *t* test will be performed to assess the difference in the measurements (the residual rates of radioactivity in the stomach at 45, 60, 75, 90, 105, and 120 min) between the TEA group and the sham-TEA group. Paired Student’s *t* test will be used to compare the differences in serum albumin, NE, TNF-α, IL-1β, IL-6, glucose, LF/HF (sympathovagal ratio), and QoL at baseline and 4 weeks after intervention in each group. The *χ*^2^ test will be used for categorical data such as the PG-SGA, HADS, and adverse events. Univariate and multivariate analyses with multiple linear regression will be used to identify independent predictors of outcome measures. The results will be aggregated as median values. *P* values of < 0.05 will be considered as statistically significant.

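### The HADS cut of over 10 is not tied to a combined or a per-domain score, and HADS is tested only as yes/no by chi-square, which discards the numeric score

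*Protocol article*

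**What the plan says.** Under Secondary outcome measures, Psychological status, the protocol article names two constructs: "Depression and anxiety symptoms will be assessed using the Hospital Anxiety Depression Scale (HADS"). It describes the instrument as a "reliable self-rating scale questionnaire with seven items (scored from 0 to 3") and gives one threshold: "A total HADS score over 10 indicates positive outcomes (moderate to severe symptoms"). No separate anxiety and depression scores or thresholds appear.

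Under Statistical analysis, the chi-square "test will be used for categorical data such as the PG-SGA, HADS, and adverse events". The outcomes compared as measurements by paired t test are "serum albumin, NE, TNF-α, IL-1β, IL-6, glucose, LF/HF (sympathovagal ratio), and QoL at baseline and 4 weeks after intervention in each group". QoL, also a questionnaire score, is in that list. HADS is not.

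The Sample size section rests on response rates of 50% and 20%, "with a two-sided significance level of 0.05", with 60 and 30 patients and a 20% allowance for losses. No mean, SD, prevalence or expected effect is given for HADS, and the Data Availability statement says that there are no baseline or pilot data.

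**The concern.** There are two separate matters.

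**Scoring.** Two constructs are named, but one item count, one total and one threshold are given. Someone scoring the questionnaire could not tell from this text which number is compared with 10, and so which patients count as positive.

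**Analysis.** The article fixes the test as well as the cut-off. A numeric score is reduced to two categories before the comparison. A patient who moves from far above the cut to just above it counts as unchanged, and one who moves by a single point across it counts as fully changed. With 60 and 30 patients there is little information to spare.

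At stake is the psychological comparison. The study objectives include psychological status, and HADS is the only instrument listed for it.

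**Working it through.** **1. What the total could be.** Seven items at 0–3 give a maximum of 7 × 3 = 21.

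| Reading | Range of the score that is cut | Are the domains merged? |
|---|---|---|
| One seven-item total, as literally described | 0–21 | Yes, one score stands for both |
| Seven items per domain, summed (assumption) | 0–42 | Yes |
| Seven items per domain, cut applied to each (assumption) | 0–21 each | No |

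The text does not decide between these. On the first two, opposite movements in anxiety and depression would partly cancel. On the third, nothing is merged.

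**2. No HADS power figure to reproduce.** The only stated power and sample size concern the response rate, so the loss has to be illustrated under assumptions.

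**3. Information kept after the cut.** Assume a normal score. For a small shift, the efficiency of the yes/no version relative to the score is φ(c)² / [p(1 − p)], where p is the share above the cut, c = Φ⁻¹(1 − p) and φ is the normal density.

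| p | φ(c) | Efficiency | Information lost |
|---|---|---|---|
| 50% | 0.399 | 0.159 / 0.25 = 0.64 | 36% |
| 30% | 0.348 | 0.121 / 0.21 = 0.58 | 42% |
| 20% | 0.280 | 0.078 / 0.16 = 0.49 | 51% |
| 10% | 0.176 | 0.031 / 0.09 = 0.34 | 66% |

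The smallest loss, 36%, occurs when the cut lies at the median.

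**4. Power at the planned size.** Inputs from the article: 60:30, two-sided 0.05, and 20% losses, which leave 90 × 0.8 = 72 patients (48:24). Assumed: a between-arm comparison, a normal score, a true difference d = 0.5 SD in favour of TEA, and the share p of sham patients above the cut.

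*t test on the score.* The noncentrality is d / √(1/n₁ + 1/n₂).
- 60:30: 0.5 × √20 = 2.236, critical t (88 df) 1.987, power 60%.
- 48:24: 0.5 × √16 = 2.000, critical t (70 df) 1.994, power 51%.

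*Chi-square on the cut.* The share of TEA patients above the cut is 1 − Φ(c + 0.5). Power is summed exactly over all pairs of binomial counts for the uncorrected test.

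| Sham above cut | TEA above cut | Power 60:30 | Power 48:24 |
|---|---|---|---|
| 50% | 30.9% | 44% | 36% |
| 40% | 22.6% | 41% | 36% |
| 30% | 15.3% | 39% | 33% |
| 20% | 9.0% | 33% | 26% |
| 10% | 3.7% | 23% | 21% |

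At 60:30, the power lost relative to the t test is 27% with half of the sham patients above the cut (1 − 0.437/0.599), 45% with 20% above (1 − 0.332/0.599), and 61% with 10% above (1 − 0.233/0.599). With a larger effect and a cut near the centre the loss is smaller: at d = 0.8 and 60% above, power falls only from 94% to 82%, a relative loss of 13%.

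**5. Baseline adjustment, a separate gain.** ANCOVA multiplies the noncentrality by 1/√(1 − r²), where r is the correlation of baseline and week-4 scores. At 60:30 and d = 0.5, r = 0.5 gives 2.582 and 72% power; r = 0.6 gives 2.795 and 79%. The values of r are assumptions. The step from 60% to 72–79% is the value of adjustment and is not part of the cost of the cut.

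**The case against.** The strongest reply is that a threshold on a questionnaire is a common way to report a secondary outcome. Subscale scoring and covariate adjustment are often left to a fuller document, and the article does not rule out also summarising the score. HADS did not drive the sample size and is not among the 1-year assessments named under Participant timeline. All of this limits the weight of the point. It does not remove it, because the article goes beyond silence: it states the cut-off and assigns HADS to the chi-square test.

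The size of the loss can also be challenged. The normal model may not fit. Mental illness and antidepressant use are exclusion criteria, so low scores bunched near zero are plausible, and the true share above the cut is unknown. This stands, and the power figures are illustrations only.

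Three stronger readings are tempting, and the article supports none of them.
- *The plan merges two outcomes.* This is the plainer reading of a single total, but a per-domain cut is compatible with the text and would merge nothing.
- *The cut costs up to half the power.* No HADS distribution or effect is given, and half is not a bound: the calculated losses run from 13% to 61%.
- *On a 0–42 scale, a cut of over 10 would not mark moderate to severe symptoms.* The article gives no severity bands, and the position of a cut within the range does not show what severity it marks.

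**Conclusion.** The point holds in a limited form. The article leaves open which score the cut of over 10 applies to, and it commits HADS to a less efficient test than the collected data allow. That the cut wastes information does not depend on which score is meant. The 36% minimum depends on approximate normality, and the power figures depend also on the assumed effect of 0.5 SD and on 20–50% of sham patients lying above the cut. The importance is low: this is a secondary outcome, and neither the primary comparison nor the sample size is affected.

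**What to change.** 1. State the number of items, the range of each score, and whether the cut of over 10 applies to a combined total or to each domain, so that the description of the instrument and the threshold agree.
2. Score anxiety and depression separately. Compare the week-4 scores between arms by ANCOVA with the corresponding baseline score as covariate.
3. Remove HADS from the chi-square list. Report the proportion above the cut in each arm as description only, naming the score and range it refers to.

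The cost is a change of wording in two sections. No extra patients or questionnaires are needed, provided that HADS is completed at baseline and week 4; the schedule figure is not visible in the text at hand, so this should be confirmed. The small downside is two HADS results instead of one, among many secondary comparisons at P < 0.05.

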##### Serum examination

The likely mechanisms of TEA are activation of somatic and peripheral nerves, anti-inflammatory effects, and functional preservation of the interstitial cells of Cajal [19]. Thus, blood will be taken for the analysis of serum norepinephrine (NE), tumor necrosis factor-α (TNF-α), interleukin-1β (IL-1β), interleukin-6 (IL-6), and glucose.

##### Quality of life (QoL)

The QoL of the patients after distal gastrectomy will be evaluated using the Short Form 36 (SF-36) questionnaire, including physical functioning, role limitations due to physical problems, bodily pain, general health perception, vitality, social functioning, role limitations due to emotional problems, and mental health. Higher scores indicate better QoL.

### Safety and adverse effects

The adverse events related to TEA or Sham-TEA will be monitored and reported by the patients themselves. It is possible to cause local events of TEA, such as skin bruising, itching, hematoma, pain, and muscular soreness, and systemic events, such as dizziness, arrhythmia, and gastrointestinal discomfort. Adverse effects will be recorded in the CRFs. The research team will provide costs of the treatment and corresponding financial compensation for these patients who suffer harm from trial participation according to the consent form.

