**Methods:**

A total of 90 eligible participants who underwent distal gastrectomy will be randomly allocated to either the TEA group (*n* = 60) or the sham transcutaneous electroacupuncture (sham-TEA) group (*n* = 30). Each participant will receive TEA on the bilateral acupoints of Zusanli (ST36) and Neiguan (PC6) for 4 weeks. The primary outcomes will be the residual rates of radioactivity in the stomach by gastric scintigraphy and total response rates. The secondary outcomes will be endoscopic features, autonomic function, nutritional and psychological status, serum examination, and quality of life (QoL). The adverse events will also be reported. The patients will be followed up 1 year after the treatment.

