## Methods/design

### Objectives and hypothesis

This study aims to (1) assess the efficacy and safety of long-term TEA for treating DGE after distal gastrectomy and (2) evaluate postgastrectomy patients by endoscopic features, autonomic function, nutritional and psychological status, serum examination, quality of life, and TEA-related adverse events. We hypothesize that TEA can safely improve DGE after distal gastrectomy.

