**Fig. 2 Fig2:**
[figure not shown]
Flow diagram of the study

All patients will undergo laparoscopic exploration with peritoneal lavage cytology to exclude peritoneal metastasis. The patients will undergo distal gastrectomy for the primary tumor, D2 or D1+ lymph node dissection with truncal vagotomy by a single clinical team. Billroth-I, Billroth-II, or Roux-en-Y reconstruction will be conducted using staplers and suture reinforcement, and Braun anastomosis will not be performed for Billroth-II reconstruction. Patients who have a high risk of recurrence will receive adjuvant chemotherapy.

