### Interventions

The researchers have been trained in the TEA technique in Pace Translation Medical Research Center, Ningbo, China, and they will teach the patients or their relatives how to implement TEA at home, with the help of a written or electronic user manual. Patients or their relatives can report adverse events by telephone or internet consultation.

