### Quality control

To guarantee the quality of the study, all researchers were well trained in the TEA technique, and the patients or their relatives were taught to implement TEA at home, with the help of a written or electronic user manual. Pictures will be taken and uploaded to our database to check the proper acupoints and frequency of TEA each day. Plans to promote participant retention and complete follow-up are as follows: First, online video calls are available for consultation to resolve any technical issues of TEA implementation and to improve research adherence of the patients. Second, we will confirm the completion of TEA each week. Third, the expenses of round trips to the hospital and relevant examinations will be reimbursed to promote participant retention. Fourth, if the participants discontinue or deviate from the trial, we will collect as much data as possible for further analysis. Researchers will be fully apprised of the inclusion and exclusion criteria, and data will be documented in CRFs. A standard operating procedure will be consistently performed according to the study protocol. Drop-outs and their reasons will be recorded. The Medical Ethics Committees will audit the procedure of the trial, have access to these interim results and make the final decision to terminate the trial.

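### Adverse event scope is worded inconsistently (device-related or all) and capture is left to patient report, so event rates will be understated and the between-arm safety comparison loses power

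*Protocol article*

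**What the plan says.** Four places in the protocol article define which adverse events count, and they do not agree.

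- **Safety and adverse effects:** "The adverse events related to TEA or Sham-TEA will be monitored and reported by the patients themselves". It then lists local events and systemic ones (dizziness, arrhythmia, gastrointestinal discomfort) and adds: "Adverse effects will be recorded in the CRFs".
- **Objectives and hypothesis:** the list of evaluations ends with "quality of life, and TEA-related adverse events".
- **Abstract, Methods:** "The adverse events will also be reported", with no restriction to related events.
- **Interventions:** "Patients or their relatives can report adverse events by telephone or internet consultation", again without the restriction, and worded as an option.

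Under Quality control, staff have a regular contact with a different stated purpose: "Second, we will confirm the completion of TEA each week". The Statistical analysis section compares arms with a χ² "test will be used for categorical data such as the PG-SGA, HADS, and adverse events". On the patients' background, the Recruitment section says: "Patients who have a high risk of recurrence will receive adjuvant chemotherapy".

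**The concern.** Safety is part of the first objective and of the hypothesis. A randomised comparison with a sham separates device effects from background illness without anyone attributing each event, provided that events are collected alike in both arms. The safety section instead restricts scope to related events and names patients as those who monitor and report.

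That matters in this population. Patients treat themselves at home, twice daily for 4 weeks, within 3–6 months of gastrectomy, and some receive chemotherapy. Dizziness and gastrointestinal discomfort are on the article's own list of possible device effects, yet the operation or chemotherapy is a ready alternative explanation. The Discussion adds that abdominal fullness, early satiety, nausea and vomiting will not be recorded, so no separate symptom record would recover such events.

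At stake are the reported event rates and the reading of a non-significant safety test, which could be taken as reassurance when events were simply not collected.

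**Working it through.** The article gives no adverse event rate, safety margin or safety power, so there is no stated figure to reproduce. The check has two parts.

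**1. The texts side by side.** Scope is related events in the objectives and the safety section, and unrestricted in the abstract and Interventions. The reporter is the patient in the safety section, and the patient or a relative in Interventions. The only regular staff contacts described, the weekly one and the daily pictures, serve completion, electrode position and frequency. The ECG on the first and last day is stated for heart rate variability.

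**2. What incomplete capture does.**

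Inputs from the article: 60 TEA and 30 sham patients; two-sided 0.05. Assumed inputs: true risks of 30% (TEA) and 10% (sham); capture fractions s from 0.3 to 1.

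*Equal capture in both arms.* The observed risk is s × the true risk. So the observed difference is s × (0.30 − 0.10), and the observed ratio is (s × 0.30)/(s × 0.10) = 3.0 for any s. Power is by exact enumeration of two binomials:

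| s | Observed TEA vs sham | Difference | Ratio | Power, Fisher | Power, uncorrected χ² |
|---|---|---|---|---|---|
| 1.0 | 30% vs 10% | 20 points | 3.0 | 0.56 | 0.60 |
| 0.5 | 15% vs 5% | 10 points | 3.0 | 0.19 | 0.25 |
| 0.3 | 9% vs 3% | 6 points | 3.0 | 0.07 | 0.08 |

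*Unequal capture.* Let the true risk be 30% in both arms.

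- Capture 60% TEA, 40% sham: 18% vs 12%, ratio 1.5 (apparent harm).
- Capture 40% TEA, 60% sham: 12% vs 18%, ratio 0.67 (apparent protection).

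With true risks of 30% vs 10%, the same two patterns give 18% vs 4% (ratio 4.5) and 12% vs 6% (ratio 2.0). The direction is not fixed.

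*Less common events.* For an assumed true risk of 5%, the chance of at least one recorded case among 60 TEA patients is 1 − (1 − 0.05s)^60: 0.94 at s = 0.9, 0.78 at s = 0.5 and 0.60 at s = 0.3.

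*Cost of counting everything.* Suppose an independent background risk b is added to 30% vs 10% and events are pooled per patient. The observed risk is 1 − (1 − p)(1 − b).

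- b = 0.20: 1 − 0.7 × 0.8 = 44% vs 1 − 0.9 × 0.8 = 28%; Fisher power 0.27.
- b = 0.40: 1 − 0.7 × 0.6 = 58% vs 1 − 0.9 × 0.6 = 46%; Fisher power 0.17.

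A single pooled all-cause comparison can therefore lose about as much power as 50% capture does.

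**The case against.** A reader might infer that only events which patients themselves consider related will ever be captured. The article does not say so. It names no judge of relatedness, recording in the CRF follows the report and could include that judgement, relatives may report too, and two of the four statements have no restriction to related events. This objection stands. What remains is that patients are the stated monitors, so an event that nobody attributes to the device has no stated prompt for being reported.

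A reader might also infer that the comparison is biased towards finding no harm. That does not follow. Patients are blinded and sham is given in the same way apart from site, so nothing in the text predicts different capture by arm. Equal under-capture leaves the risk ratio alone, and unequal capture can push either way.

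Nor would every unattributed event necessarily be missed. Telephone, internet and video consultation exist, the ECGs might show an arrhythmia, and reasons for drop-out are recorded. None of these, however, is a scheduled question about adverse events.

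Power is modest even with full capture (0.56 to 0.60 on the assumed risks), so a non-significant result would be inconclusive in any case. This also stands, and it bears on how the result is reported.

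Finally, this is a condensed article, and event forms and causality procedures may sit in the full protocol. Their absence here is not held against the plan. The criticism is of the wording that the article does fix, and of its inconsistency.

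**Conclusion.** The point holds in a limited form. The article contradicts itself on which adverse events are in scope, and its most specific statement describes related-only, patient-dependent capture for an outcome that belongs to the first objective. Followed as written, it would understate absolute event rates and reduce the power of the between-arm test. On the assumed risks of 30% vs 10%, halving capture takes Fisher power from about 0.56 to 0.19 and the risk difference from 20 to 10 points, with the ratio unchanged at 3.0.

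These sizes rest wholly on assumed risks and capture fractions. They show the mechanism and are not a forecast for this trial. The direction is firm for the absolute rates, and for the risk difference and power under equal capture. It is not firm for the risk ratio or under unequal capture. The change is worth making while recruitment continues, because events not asked about at the time cannot be reliably recovered later.

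**What to change.** - Reword the safety section, and align the objectives with it, so that all adverse events from the first session to week 4 are recorded regardless of attribution.
- Ask about them with the article's own event list at the existing weekly contact and at week 4, in identical words in both arms.
- Have an existing investigator who is blind to arm judge relatedness afterwards.
- Report by arm and event type both all events and events judged related, with risk differences and confidence intervals. State that a non-significant test is not evidence of safety.

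The cost is a short checklist at a contact that already takes place, more records to enter, and higher reported rates in both arms. The all-cause comparison will also be diluted by background events, as shown above. For that reason the event-type and related-event tables should stand beside it, and pooled all-cause events should not be the only primary safety comparison.
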